#### Cost assessment

To evaluate the economic consequences of NPRL2.0 from a societal perspective, as recommended by the Dutch guidelines for costing studies in healthcare, the intervention costs, other healthcare costs, patient and family costs, and productivity losses will be assessed [48].

The intervention costs include costs of education meetings for healthcare professionals and peer review meetings for the intervention group, and consulting and/or treatment hours for the intervention and control groups. The education costs are for 2 × 3 h of education and 1 × 3 h of additional education for therapists. For each education session, the costs of two teachers and one meeting room will be taken into account. These costs will be charged at 10% per patient as it is assumed that healthcare professionals need education only once. Multidisciplinary consultations are organized with all healthcare professionals of the local networks in the absence of patients. For the multidisciplinary consultations per patient, the costs of the healthcare professionals will be divided by six, assuming that during one hour the status of six patients will be discussed. Moreover, it will be assumed that on average each patient is discussed during three multidisciplinary consultations. The number of consultations and/or treatment hours will be collected by the research team from the records of the patients in both the intervention and control groups. To calculate costs for healthcare professionals, standardized cost-prices as prescribed in the Dutch manual for cost-analysis in healthcare research will be used [48].

Healthcare usage will be measured with the iMTA Medical Consumption Questionnaire (iMCQ). It contains questions about healthcare consumption related to frequently-occurring contacts with healthcare professionals (www.imta.nl). The iMCQ will be combined with the iMTA Productivity Cost Questionnaire (iPCQ), a standardized instrument suitable for self-completion by patients for measuring and valuing all relevant productivity losses of paid and unpaid work for use in economic evaluations [61]. The manual for the iMCQ and iPCQ will be used for evaluating healthcare usage and productivity losses with the friction cost approach. The costs of prescribed medication will be calculated by multiplying the number of tablets that participants used during 3 months with the cost price as described at the Dutch webpage https://www.medicijnkosten.nl; the pharmacist costs will also be included. For over-the-counter medication, the lowest prices of Dutch drugstores and pharmacies will be used. All costs will be given in euros and, when necessary, indexed using the general Dutch Consumer Price Index rates [62].

Besides the iPCQ and iMCQ, the patients will be asked about their current care status and the treatment program for their CMP complaints. Moreover, at the end of the study, participating practices and rehabilitation centers will use the records of the patients to collect data about the length, content, and duration of the program.

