#### Integral focus on self-management: eHealth application

Healthcare professionals and patients participating in the NPRL2.0 will make use of the eHealth application: SanaCoach Pain Rehabilitation [38]. The coach's primary goal is to support self-management. Its main function is to provide module-based pain education. Different eLearning modules are developed for the patients in order to teach them about the biopsychosocial aspects of pain. In addition, diaries are integrated in which patients can provide information on their pain intensity, level of activity, mood, and participation level. Moreover, healthcare professionals can use scores from these diaries to adjust treatment protocols to the needs of individual patients. The application also consists of a chat function between the patient and their healthcare professionals to ensure prompt communications. The functions in the SanaCoach Pain Rehabilitation, such as the number of diaries and the level of education, will be adapted to the patient, based on his/her complexity and level of disability.

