#### Education and collaboration

Healthcare professionals will receive education during the 3-month wash-out period: GPs 2 × 3 h and therapists 3 × 3 h. Topics in the education program include biopsychosocial theories of CMP, recognition of patients with or at risk of CMP, providing education to patients with CMP, use of the assessment tool and eHealth application, and treatment selection. The first two sessions are organized jointly for all disciplines of healthcare professional in order to promote a common understanding of biopsychosocial treatment. Separately, therapists will also receive information about the treatment protocols. To encourage collaboration in the local networks, three additional peer-review meetings of one hour (every 6–8 weeks) are organized by the project team in each local network after the wash-out period. During these meetings, healthcare professionals apply the theories and treatment protocols learned during the education program in daily practice, with room for extra education by the teachers if necessary. After these three peer-review meetings, the local networks are encouraged to organize further such meetings in order to align the working procedures and treatment plans of the patients.

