### Sample size

In the prospective cohort, all patients with CMP who visit the two local networks of NPRL1.0 will be invited to participate in the study. Based on the recruitment results of the feasibility study of NPRL1.0, and the number of patients visiting a GP practice, we expect that each local network will also recruit about six patients per month. Therefore, the two local networks from NPRL1.0 together should recruit approximately 132 patients in 11 months. Assuming a dropout rate of 20%, we expect to include approximately 105 patients in this study.

To calculate the desired sample size for the stepped-wedge based design, we used the method described by Woertman et al. [39]. The calculations of the number of patients needed are based on the primary outcome of the cost-utility analysis, the health-related quality of life measured with the 5-level EQ-5D version (EQ-5D-5L). Based on McClure et al., we consider an increase of 0.063 points (SD = 0.013) in 1 year as clinically relevant [40]. In addition, an alpha of 0.05, a power of 80%, a 1:1 ratio between control and intervention groups, and a dropout rate of 30% were assumed. Based on these values and the stepped-wedge based design, a design effect (DEsw) of 0.416 exists, which leads to a required sample size of 184 patients (92 control and 92 intervention). Based on the recruitment results of the feasibility study of NPRL1.0, and the number of patients visiting a GP practice, we expect that each local network will recruit 6 patients per month [32]. Therefore, with a dropout rate of 30% of local networks, six local networks will need to participate.

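### The base-case intervention cost leaves out professionals' training time and the eHealth application, and the 10%-per-patient education charge needs a defined denominator

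*Protocol article*

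**What the plan says.** The Cost assessment section sets out "To evaluate the economic consequences of NPRL2.0 from a societal perspective". It describes the intervention cost as follows: "The intervention costs include costs of education meetings for healthcare professionals and peer review meetings for the intervention group, and consulting and/or treatment hours", the last item for both groups. On education it says "For each education session, the costs of two teachers and one meeting room will be taken into account", and then "These costs will be charged at 10% per patient as it is assumed that healthcare professionals need education only once". For multidisciplinary consultations, the same section does count the professionals' own cost, divided by six patients per hour and charged three times per patient.

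The Intervention section presents the eHealth application as one of the elements of NPRL2.0 primary care: "Healthcare professionals and patients participating in the NPRL2.0 will make use of the eHealth application". The Education and collaboration section gives the training load as two 3-hour sessions for GPs and three for therapists, with the first two sessions held jointly for all disciplines.

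The Data analysis section plans four one-way sensitivity analyses: the education cost, the multidisciplinary consultation cost, over- or under-reporting in the iMCQ, and SF-6D in place of EQ-5D-5L. It acknowledges that the intervention cost may be too high because training is needed only once.

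**The concern.** Incremental cost is the numerator of both the ICER and the ICUR. Two resources that NPRL2.0 uses and usual care does not are missing from the cost list: the hours professionals spend in training, and the application. From a societal perspective both are costs of the intervention. The section is also inconsistent, since it values professionals' time in multidisciplinary consultations but not in education.

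The 10% rule raises a separate problem. A one-off training cost should be spread over the patients who benefit from it. A fixed 10% charge to every patient does that only if each training series serves exactly 10 patients, and the plan expects more.

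Bootstrapping will not reveal either problem, because it describes sampling uncertainty around whatever cost definition is used.

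**Working it through.** The plan states no euro amount for the intervention, so there is no cost figure to reproduce. The check is in hours and in shares of one education series.

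**Inputs**
- GP training 6 h, therapist training 9 h, first two sessions joint (Education and collaboration).
- At least one therapist, one GP and one mental health nurse per network; two networks in each of three steps; intervention periods of 5, 4 and 3 months for groups A, B and C (Study design).
- Two teachers per session; 10% of education cost per patient (Cost assessment).
- 92 intervention patients, six networks, 30% dropout, and "we expect that each local network will recruit 6 patients per month" (Sample size).
- Assumption: the nurse attends the two joint sessions (6 h). The article gives no hours for nurses.

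**1. Training time**
- Costed teacher time for one series: 2 teachers × (2 × 3 h + 1 × 3 h) = 18 h.
- Attendee time not costed, per network at minimum staffing: 6 h (GP) + 9 h (therapist) + 6 h (nurse) = 21 h.
- If the two networks in a step share one series: 2 × 21 = 42 attendee-hours against the same 18 teacher-hours. Larger networks widen the gap.

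**2. eHealth application**
- Intervention element: yes. Listed intervention cost: none. Sensitivity analysis that adds it: none of the four. The article gives no price, so this omission cannot be sized.

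**3. The 10% charge, read literally**

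Share of one series recovered = 10% × patients served by that series. Break-even is 1 / 0.10 = 10 patients.

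| Basis | Patients per network | Share recovered, one series per network |
|---|---|---|
| 92 / 6 | 15.3 | 153% |
| 92 × 0.7 / 6 | 10.7 | 107% |
| 6 per month × 3 months (group C) | 18 | 180% |
| 6 per month × 4 months (group B) | 24 | 240% |
| 6 per month × 5 months (group A) | 30 | 300% |

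If one series serves the two networks of a step, 92 / 3 = 30.7 patients, so 307%. If one series served all six networks, it would be 920%.

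The per-patient charge that just recovers the cost over 92 patients is 1 / 15.3 = 6.5% (series per network), 1 / 30.7 = 3.3% (per step) or 1 / 92 = 1.1% (all networks).

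**4. The 10% charge, read as depreciation**

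If 10% of the cost is attributed to the study and then shared, each patient carries 10% / 15.3 = 0.65% of a network's series. The two readings differ by a factor of 15.3 in the education cost per patient.

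**5. Does the result depend on the 92?**

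The stated inputs do not reproduce the 184. With a difference of 0.063 and SD 0.013, the standard two-sided formula gives 2 × (0.013 × 2.80 / 0.063)² = 0.67, that is 1 patient per arm before any adjustment. That is a separate matter. The recruitment rate alone gives 18–30 patients per network, or 12.6–21 after 30% loss (126–210%), so the literal over-recovery does not rest on the 92.

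**The case against.** **The list may not be exhaustive.** The verb used is include, and an article condenses a full protocol that is not shown. A licence or hosting fee could sit there, and clinicians' use of the application may already fall within treatment hours. This has some force for the application fee. It has less for training time: the section goes down to teachers and a meeting room per session, and counts professionals' cost for consultations a few sentences later.

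**The 10% may be depreciation.** The stated reason, that education is needed once, fits that reading. This stands. A reader might infer that over-recovery is proven, but the wording permits both readings. Under depreciation, though, charging per patient is the wrong description.

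**The plan already concedes a possible overestimate and tests it.** True for the size of the education cost. The planned analysis tests the influence of including it and states no corrected allocation. It does not reach the two omissions. The Discussion also frames the cost hypothesis without educational costs. That comparison escapes the 10% rule and the attendee-time gap, but not the missing application cost.

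**Consultations.** A reader might infer a further contradiction, since "it will be assumed that on average each patient is discussed during three multidisciplinary consultations" while the project team organises only "three additional peer-review meetings of one hour" per network. The document does not support this. It never equates the two activities, it encourages networks to hold further meetings, and it says that the number of patients discussed is unknown and tests that cost.

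**Conclusion.** The point holds for the two omissions and, more conditionally, for the 10% rule. Followed as written, the base case leaves out about 21 attendee-hours per network (minimum staffing, nurse at both joint sessions) against 18 teacher-hours counted, and leaves out the application altogether. No planned sensitivity analysis would show the effect of either.

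The 10% rule, read literally, charges 107–300% of a network's education cost across the plan's own patient numbers, and more if networks share sessions. Read as depreciation it does not over-recover. With a 15-fold difference between readings, the rule has to be defined before analysis.

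It would be tempting to conclude that NPRL2.0 is made to look too cheap, or too dear. Neither follows: the omissions lower the intervention cost, the literal charge raises it, and there are no unit prices with which to net them. This is a matter of costing definition; no stated total is miscalculated.

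**What to change.** In the base case:
- Value attendees' training hours, from attendance by discipline, at the standard cost prices the plan already uses for professionals.
- Add a per-patient cost for the eHealth application, and state whether clinicians' time on it is already within treatment hours.
- Replace the 10% rule with total education cost (teachers, room and attendees' time) divided by a stated number of patients treated by the trained networks. The minimum is the trial's intervention patients. A larger number, reflecting use after the trial, needs a stated justification, since the document gives no useful life for the training.
- Vary that denominator in the education sensitivity analysis already planned.

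Also state whether peer-review meetings and multidisciplinary consultations are the same activity, because both appear as costs and could be counted twice.

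The price is revised costing text, a little more costing work and obtaining the application fee. Patients, visits and questionnaires are unaffected.

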#### Learning curve

Data regarding the background experience and knowledge of healthcare professionals will be assessed at the start of the study to judge whether there is a learning curve when participating in NPRL2.0. Whether patient outcomes regarding health and costs are improved when healthcare professionals have more experience of and knowledge about treating patients with CMP will be assessed.

The Pain Attitudes and Beliefs Scale (PABS) will be used to measure clinicians’ biomedical and biopsychosocial treatment orientations with respect to back pain [63]. It consists of 36 statements about treatment preferences, scored on a six-point Likert scale (from 1 = ‘totally disagree’ to 6 = ‘totally agree’). The sum score ranges from 6 to 60 for the biomedical factor and 6 to 54 for the biopsychosocial factor [64]. The PABS shows a consistent factor structure and good test–retest reliability and construct validity [65].

### Data analysis

Demographic data (e.g. gender, age, home situation, level of education, nationality, and co-morbidities) will be described overall and separately for the intervention and control groups. Frequencies are to be presented for categorical variables, means and standard deviations (SDs) for normally-distributed continuous variables, and medians and ranges for non-normally-distributed continuous data. The two groups will be tested on differences between characteristics, using the *t*-test for continuous variables and the chi-squared test for categorical variables. If variables differ between the two groups, with *p* ≤ 0.10, they are considered to be potential confounders in further analyses.

Outcomes on questionnaires will be compared using linear mixed-model analysis, to take into account repeated measurements in patients as well as the effects of the clustering of patients within local networks. The fixed part of the model contains treatment group (intervention/control), time, treatment group*time, and cluster (local network). To assess the learning effect in local practices, the time (months) that a local network participates in NPRL2.0 will also be taken into account as a fixed variable. Variables known to be related to the outcome and differing between treatment groups at T1 (*p* ≤ 0.10) will be added to the model. An unstructured covariance structure will be used for repeated measures. Missing values for items in the questionnaires will be handled according to the scoring algorithms of the questionnaires. Missing variables in the follow-up data will not be imputed because linear mixed-model analysis is a flexible method for handling missing data for stepped-wedge and repeated-measures designs (likelihood-based approach). Linear mixed-model analyses will be performed using IBM SPSS Statistics for Windows (version 24.0 or higher, Armonk, NY: IBM Corp.) according to the intention-to-treat principle. Other missing values for non-repeated measures will be handled by multiple imputation, which means that missing values will be predicted using existing values for other variables [66].

Costs will be compared using bootstraps (1000 replications) with Microsoft Excel 2016 with mean differences and 95% confidence intervals. Subsequently, sample uncertainties around the incremental cost-effectiveness ratio (ICER) and incremental cost-utility ratio (ICUR) will be explored using bootstrapping with a minimum of 5,000 replications. The ICER and ICUR will be defined by the difference in costs between NPRL2.0 and the control group, divided by the difference in incremental effects of the SF-12 and incremental QALYs respectively. Cost-effectiveness analyses will be performed with the mean total costs and the mean SF-12 scores. The cost-utility analysis will be performed by relating the mean total costs to the mean QALY scores of both groups, and the bootstrapped ICURs will be plotted in cost-effectiveness planes. Moreover, uncertainties of the ICERs and ICURs will be graphically presented in cost-effectiveness planes (CE plane), as well as cost-effectiveness acceptability curves (CEAC). A CEAC will be calculated to describe the probability of NPRL2.0 being a cost-effective alternative to the control group [67]. This CEAC includes the amount of money the society is willing to pay (WTP) in order to gain one unit of effect (one QALY here). The WTP threshold in the Netherlands for one QALY is based on the health burden and varies between €20,000 (health burden 0.1 to 0.4), €50,000 (health burden 0.41 to 0.7) and €80,000 (health burden 0.71 to 1) (2015) [68].

Four sets of sensitivity analyses will be performed to measure the robustness of the economic evaluation. These analyses will explore the impact of an assumption on the results when changing one value of one parameter while keeping all the other parameter values unchanged [69]. One sensitivity analysis will be performed to measure the influence of taking the educational costs included the intervention costs. Because healthcare professionals will only need training once, the intervention costs may be overestimated. The secondary sensitivity analysis will be performed to assess the influence of the multidisciplinary consultation costs. No standard cost price exists for multidisciplinary consultations in primary care in the Netherlands and it is not known how many patients will be discussed in order to be able to split the costs over these patients. The tertiary sensitivity analysis will be performed to see if there is over- or under-reporting of healthcare consumption in the iMCQ. The data from the records regarding GP and therapist sessions will be compared with the patient data from the iMCQ. When over- or under-reporting is found, a secondary cost analysis will be performed with corrections on all healthcare consumption data, assuming that the same amount of over- or under-reporting is present in the iMCQ. In a fourth sensitivity analysis the impact of the SF-6D to calculate QALYs instead of the EQ-5D-5L will be assessed.

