## Methods

### Study design

In this pragmatic study, the recruiting period will be from April 2019 till March 2020, with follow-ups till December 2020. This study comprises two designs; a prospective cohort study and a stepped-wedge based design.

Two local networks of NPRL1.0 will be enrolled in NPRL2.0. They will receive additional education and information based on the results of the feasibility study of NPRL1.0. In NPRL2.0, they will invite patients to participate in a prospective cohort study.

In the stepped-wedge based design working according to NPRL2.0 will be introduced in three steps in two local primary care networks at the same step (step A, B or C). Local networks that intensively collaborate, due to their geographical location, will be placed together in one step (A, B or C). An independent research assistant will randomly allocate the local networks over the steps. In one local network, at least one therapist, general practitioner (GP), and mental health nurse will participate. Each local network will first recruit patients as controls during a period of care as usual, followed by a 3-month ‘wash-out’ period in which education is given (see Fig. 1). After the wash-out period, a local network will then recruit patients during the intervention period in which NPRL2.0 is the standard of care. According to the stepped-wedge based design, length of control and intervention periods vary in each group: Group A will spend 3 months as control and 5 months with intervention; for Group B, there will be 4 months as control and 4 months with intervention; and Group C will spend 5 months as control and 3 months with intervention. Thus, healthcare professionals in all local networks will recruit patients for participation in both control and intervention groups. Patients will contribute data to either the control group or the intervention group, but not both. A stepped-wedge based design is the most feasible design in this pragmatic study as it has the following advantages: (1) it controls for between-local network variation in daily practice; (2) it gives the opportunity to assess intervention effects in a pre/post comparison across local networks, which increases statistical power; (3) it gives an opportunity to assess learning effects by comparing the results of local networks that transit earlier with those that transit later [34].

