## Discussion

The Network Pain Rehabilitation Limburg 2.0 (NPRL2.0) has been developed in order to provide integrated care with a biopsychosocial approach for people with CMP with the goal of improving their level of functioning. Moreover, it is intended to accomplish the Quadruple Aim: improvement of pain-related disability of people with CMP; improvement of experiences of care of people with CMP; improvement in the meaning of work for healthcare professionals; and the reduction of healthcare costs of people with CMP. In this quantitative study, the effectiveness of NPRL2.0 in reducing the pain-related disability of people with CMP will be assessed. In addition, the influence of NPRL2.0 on healthcare costs will be examined with a cost-effectiveness and cost-utility analysis. Moreover, the learning curve of healthcare professionals working in NPRL2.0 will also be studied.

NPRL2.0 is a multidimensional, complex intervention, executed in daily practice [33]. Because of the practice-based approach of this study, a randomized controlled trial design (RCT) is not suitable. Therefore, a pragmatic study with stepped-wedge based design using randomization of the local networks was seen as a viable alternative to an RCT [70]. The local primary care networks involved would be randomly assigned to the three steps (A, B or C) in order to randomize the duration of being a control group or intervention group. Local networks are their own controls in a stepped-wedge based design. Healthcare professionals are instructed to recruit patients at their first consultation for CMP complaints. Therefore, it is expected that patients with comparable complexities of complaints will be distributed equally over the control and intervention groups. Moreover, in this practice-based research, connections between science, policy, and practice exist during implementation and execution of NPRL2.0, leading to evidence-based practice. The external validity of the results of such as this pragmatic study of NPRL2.0 is commonly higher than that of RCTs because the results are more generalizable.

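### Control and intervention recruitment never share a calendar month and the model has no calendar-time term, so the randomised steps cannot separate NPRL2.0 from period

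*Protocol article*

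**What the plan says.** **Timetable (Methods, Study design).** Every network recruits controls first, "followed by a 3-month ‘wash-out’ period in which education is given", and then recruits intervention patients. The shortest control period is at one end of the schedule: "Group A will spend 3 months as control and 5 months with intervention". The longest is at the other: "Group C will spend 5 months as control and 3 months with intervention". The middle group has four months of each. For the calendar, "the recruiting period will be from April 2019 till March 2020, with follow-ups till December 2020". A patient belongs to one condition only, so the date of inclusion fixes the group.

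**Model (Methods, Data analysis).** "The fixed part of the model contains treatment group (intervention/control), time, treatment group*time, and cluster (local network". The months a network has taken part in NPRL2.0 enter as a further fixed variable, to capture learning. Covariates related to the outcome that differ at T1 with p ≤ 0.10 are added. No calendar month, season or step term is listed.

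**Economic analysis (same section).** Costs are compared by bootstrapped mean differences, and the ICER and ICUR use group means. No adjustment for period or network is stated, and none of the four sensitivity analyses concerns period.

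**Interpretation (Discussion).** The design, with randomisation of networks, is presented as a viable alternative to a randomised trial, and "Local networks are their own controls in a stepped-wedge based design".

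**The concern.** A stepped wedge separates treatment from period because, in some months, some networks are still in control while others have already crossed over. Randomising the order of crossing makes that concurrent comparison fair. Here the steps are one month apart and the wash-out lasts three months, so the concurrent months may be missing altogether. If they are, each network contributes a before-after difference: recruitment from April 2019 onwards against recruitment in the last months of the window. A change in who presents, in referral, in prices or in season could then be read as an effect of NPRL2.0, or could hide one, and randomising the steps would give no protection. The PDI result, the SF-12 result and the QALY and cost differences would all be affected, though not equally.

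**Working it through.** The plan gives no figure on this point to reproduce. The check rebuilds the timetable and then the design matrix.

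**1. Timetable.** Inputs are the durations above. A common start in month 1 is inferred: each sequence fills 11 months (3+3+5, 4+3+4, 5+3+3), all networks begin in control, and the window is April to March.

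| Group | Control | Wash-out | Intervention | Mean control month | Mean intervention month | Gap |
|---|---|---|---|---|---|---|
| A | 1-3 | 4-6 | 7-11 | 2.0 | 9.0 | 7 |
| B | 1-4 | 5-7 | 8-11 | 2.5 | 9.5 | 7 |
| C | 1-5 | 6-8 | 9-11 | 3.0 | 10.0 | 7 |

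The longest control period ends in month 5 and the earliest intervention period starts in month 7, so the overlap is empty (24 control and 24 intervention network-months). If Group C started s months later, overlap with Group A would need 5 + s ≥ 7, that is s = 2. Group C would then end in month 13, outside even a 12-month window. At each visit the groups are also disjoint: T1 falls in months 1-5 against 7-11, and T4 in months 10-14 against 16-20.

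**2. Estimability.** Take one row per network-month, with 6 networks and 10 recruiting months (month 6 has none). Network plus month categories has 6 + 9 = 15 columns and rank 15. Adding treatment gives 16 columns, still rank 15, because treatment equals the sum of the indicators for months 7-11. Treatment is therefore not estimable with month categories.

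**3. Size of a drift of b per month.**
- Network and treatment only: the coefficient is the within-network gap, 7b.
- With participation months coded 1, 2, ...: 4.6b on treatment and 0.95b per month on learning. Coding at mid-month (0.5, 1.5, ...) gives 5.1b and 0.95b.
- Pooled means without network terms: intervention (10×9 + 8×9.5 + 6×10)/24 = 226/24, control (6×2 + 8×2.5 + 10×3)/24 = 62/24; the difference is 164/24 = 6.8b.

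On the 0.063 utility difference in the Sample size section, the drift that would create the whole effect is 0.063/7 = 0.009 per month, or 0.063/4.6 = 0.014 with the participation term. These figures show leverage; the documents give no estimate of any drift.

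**4. Which contrast is exposed.** Fit group, visit, group-by-visit and network to artificial trends:
- Linear calendar trend: 7b on the group main effect, 0 on every group-by-visit term.
- Stable case-mix shift after month 5: passes one-for-one to the main effect, 0 on group-by-visit.
- 12-month seasonal cycle of amplitude a: up to 1.6a on the main effect and up to 2.2a on group-by-T4.
- Step change at study month 15 or 16: passes one-for-one to group-by-T4.

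**5. Price of a calendar term.** Variance of the treatment coefficient, with unit residual SD and 6 patients per network-month (the recruitment rate in the Sample size section):

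| Model | Without participation term | With it (coded 1, 2, ...) |
|---|---|---|
| Six networks, no calendar term | 0.0145 | 0.0435 |
| Six networks, linear month | 0.1346 | 0.1434 |
| Six networks, month categories | not estimable | not estimable |
| Plus two cohort networks as always treated, month categories | 0.0502 | 0.2327 |

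Ratios for the linear term: 0.1346/0.0145 = 9.3 and 0.1434/0.0435 = 3.3.

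**The case against.** **A reader might infer that any secular or seasonal shift will be reported as the NPRL2.0 effect.** The documents do not support that. The model contains group-by-time, and if the effect is read as change from T1, a linear trend or a stable case-mix difference cancels. Adjustment for variables that differ at T1 also removes some measured case-mix. This stands, within limits: seasonal and step changes do not cancel, the article does not say which coefficient is the effect, and the cost and QALY mean differences have no such protection.

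**A reader might also infer that the article promises control over calendar time and fails to deliver it.** It does not promise this. Study design claims control of between-network variation, a pre/post comparison and a view of learning. The network term delivers the first, and the statement that networks are their own controls is true. What remains is that randomised steps are offered as the substitute for a randomised trial without saying that period is uncontrolled.

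**Participation months might serve as a calendar term.** If they were counted from the start of the study they would. The stated purpose, learning, makes NPRL2.0 exposure the more natural reading. On the calendar reading, the 9.3-fold variance applies.

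**Drift of this size is unlikely.** A rate of 0.009 per month is 0.108 per year, 2.7 times the 0.04 minimal important change that the article gives for the EQ-5D-5L. That is fair as to a smooth trend. A seasonal, step or case-mix change need not be smooth, and a smaller shift would still bias the result.

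**The timetable figure is not shown.** True. The common start is inferred, but no staggering that fits the window creates overlap.

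**Conclusion.** The point holds. On the stated durations, control and intervention inclusion share no calendar month, the fixed part has no calendar term, and randomising networks to steps cannot separate NPRL2.0 from period. The exposure is greatest for the group main effect and for the cost and QALY mean differences. For group-by-time it is limited to seasonal, step and other non-linear changes. The 7b and 4.6b figures assume a linear drift and even recruitment; 4.6b also depends on how participation months are coded. A calendar term does not fully repair this: month categories fail in the six networks, and a linear term rests on extrapolation across the gap. The conclusion relies on the inferred common start and on reading *time* as follow-up time (T1-T4). If *time* meant calendar month as categories, treatment would be aliased with it.

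**What to change.** 1. **Relabel.** In Study design and Discussion, describe the comparison as a staggered, within-network before-after comparison, and say that randomising the steps does not protect it from period effects. Interpret the results in those terms. Cost: wording only.

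2. **Add a pre-specified calendar-time sensitivity analysis beside the stated model, and for costs and QALYs too.** Use the inclusion (T1) dates, from which T2-T4 are scheduled anyway. Two forms are workable: a linear or seasonal inclusion-month term in the six networks; or month categories with the two cohort networks fitted as an always-treated sequence. The second must state its assumption that calendar trend and learning are common to the stepped-wedge networks and to non-randomised cohort networks with NPRL1.0 experience.

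No new data are needed. The downside is wider, model-dependent intervals. With month categories and the cohort, the variance is 0.050 without the participation term (3.5 times 0.0145) and 0.233 with it (5.3 times 0.0435). The recruitment window was due to close before the article appeared, so the remedy lies in analysis and interpretation, not in the timetable.
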